## Abstract

**Background:**

Quality of life (QoL) decreases as heart failure worsens, which is one of the greatest worries of these patients. Physical exercise has been shown to be safe for people with heart failure. Previous studies have tested heterogeneous exercise programs using different QoL instruments and reported inconsistent effects on QoL. The aim of this study is to evaluate the effectiveness of a new exercise program for people with heart failure (EFICAR), additional to the recommended optimal treatment in primary care, to improve QoL, functional capacity and control of cardiovascular risk factors.

**Methods/Design:**

Multicenter clinical trial in which 600 patients with heart failure in NYHA class II-IV will be randomized to two parallel groups: EFICAR and control. After being recruited, through the reference cardiology services, in six health centres from the Spanish Primary Care Prevention and Health Promotion Research Network (*redIAPP*), patients are followed for 1 year after the beginning of the intervention. Both groups receive the optimized treatment according to the European Society of Cardiology guidelines. In addition, the EFICAR group performs a 3 month supervised progressive exercise program with an aerobic (high-intensity intervals) and a strength component; and the programme continues linked with community resources for 9 months. The main outcome measure is the change in health-related QoL measured by the SF-36 and the Minnesota Living with Heart Failure Questionnaires at baseline, 3, 6 and 12 months. Secondary outcomes considered are changes in functional capacity measured by the 6-Minute Walking Test, cardiac structure (B-type natriuretic peptides), muscle strength and body composition. Both groups will be compared on an intention to treat basis, using multi-level longitudinal mixed models. Sex, age, social class, co-morbidity and cardiovascular risk factors will be considered as potential confounding and predictor variables.

**Discussion:**

A key challenges of this study is to guarantee the safety of the patients; however, the current scientific evidence supports the notion of there being no increase in the risk of decompensation, cardiac events, hospitalizations and deaths associated with exercise, but rather the opposite. Safety assurance will be based on an optimized standardised pharmacological therapy and health education for all the participants.

**Trial Registration:**

Clinical Trials.gov Identifier: NCT01033591

## Background

Heart failure (HF) affects more than 15 million people out of the 900 million who live in the 51 countries represented in the European Society of Cardiology [1]. In Spain it occurs in 1-2% of individuals older than 40 years old and in 10% of those over 60 [2]. It is also the first cause of hospital admission and involves a yearly expenditure of four thousand million Euros for health services [3]. Although survival rates of people with HF have increased with the current pharmacological treatments, this does not necessarily entail an improvement in quality of life [4]. Quality of life worsens with increasing severity of HF. This is one of the greatest concerns of such patients and some studies suggest that it is a predictive variable for the progress of disease, independently of other prognostic factors, such as left ventricular ejection fraction [5,6]. Non-pharmacological interventions, such as physical exercise may have a great impact on the quality of life, but this remains poorly studied. In particular, the studies carried out have used very heterogeneous exercise programmes, have evaluated quality of life in very different ways and have reported inconsistent results [7].

Among the current recommendations, there are no clear guidelines about the type, intensity, duration and progress of exercise programmes that should be carried out by people with HF [8,9]. Also, the minimum exercise required still remains unknown, let alone what are the optimum conditions. For this reason primary care doctors only give these patients the general advice of walking at least 30 minutes per day, preferably every day of the week [10]. Reviewing the opinion of various authors and looking at recent studies that advocate high-intensity interval training, the ideal would be to evaluate an exercise programme that covers the following aspects: (1) short bursts of high-intensity aerobic exercise; (2) exercise combined with building strength/stamina; (3) supervised initially in the health centre, for the intervention to be adapted to each patient and to guarantee adherence; and (4) linked to resources external to the health service in the community or in the home of the patient, to achieve long-term continuity [11-15]. An intervention of this type would be innovative and could be highly effective, given that it brings together the scientific evidence of previous interventions that have been shown to be hypothetically effective.

On the other hand, physical exercise per se has been shown to be a safe intervention for people suffering from HF. This assertion has been supported by the recent HF-Action study, the largest clinical trial carried out on 2331 people with HF in NYHA class II-IV, to evaluate the effect of aerobic exercise in such patients [16,17]. The study concluded that exercise has a small beneficial effect on mortality and hospital admissions. Based on this study, it is plausible to hypothesise that the great contribution of exercise may be reflected in functional capacity and quality of life. In this study, the "state of health" (quality of life, symptoms, physical and social limitations) greatly improved in only three months. At the time the difference between the groups for comparison was not considered to be clinically relevant and only a small effect, of less than two points, could be attributed to exercise. In subsequent follow-ups, this limited difference remained constant, throughout the three years of monitoring [16]. The authors admitted that the lack of further improvement in scores after three months may have been a reflection of the exercise intervention not having been optimal, and the fact that the long-term adherence to the exercise programme was low and that the usual care group increased its physical activity.

## Objectives

To evaluate the effectiveness of a progressive exercise programme (high-intensity interval + strength training), in addition to optimal pharmacological and non-pharmacological treatments, to improve the health-related quality of life of those suffering from class II-IV heart failure, their functional capacity and prognosis.

### Main objective

- To estimate the improvement of health-related quality of life in patients involved in the EFICAR programme and the control group, and also any difference between the two groups in terms of improvement in quality of life, which would be an effect that could be attributed to exercise.

### Secondary objectives

- To estimate the improvement in functional capacity, control of risk factors and prognostic factors in the EFICAR and in the control group, and also any difference between the two groups, that could be attributed to exercise.

- To estimate any changes in the effect of exercise as a function of the various subgroups of age, sex, risk factors and co- morbidity.

## Methods/Design

### Study design

This is a multicenter, randomized, controlled clinical trial, in which people suffering from Heart Failure (HF) are assigned to two parallel groups: the EFICAR group (exercise + optimised usual care) and control group (only optimised usual care).

The candidates to be included in the study go through two consecutive phases: 1^st ^phase of "therapy optimisation" prior to inclusion in the study, and 2^nd ^phase of "monitoring and evaluation of results". Both groups are subject to a series of standardised elements of care: optimised pharmacological treatment, health education and support for the development of self-care. Patients are monitored for 3, 6 and 12 months. Blind measurements of quality of life, functional capacity and risk factors are repeated three times (see Figure 1).

**Figure 1 F1:**
[figure not shown]
**Algorithm of the study**.

### Settings

Six primary health centres, part of the Spanish Primary Care Prevention and Health Promotion Research Network (*redIAPP*), henceforth referred to as the redIAPP network, were selected, accredited and financially supported the Carlos III Health Institute:

- Basauri-Ariz Health Centre. Basque Health Service - Osakidetza. Bizkaia. Spain.

- Galdakao Health Centre. Basque Health Service - Osakidetza. Bizkaia. Spain.

- La Alamedilla Health Centre. Castilla y León Health Service. SACYL. Salamanca. Spain.

- Sant Roc Health Centre. ICS. Catalan Health Service. Barcelona. Spain.

- Casa de Barco Health Centre. Castilla y León Health Service. SACYL. Valladolid. Spain.

- Calviá Health Centre. Balearic Islands Health Services. IBSALUT. Mallorca. Spain.

Each collaborating centre has an established logistical structure, derived from the undertaking of the "Multicentric Assessment of Experimental Programme of Physical Activity (PEPAF)" research project. This structure is composed of:

- A laboratory for measuring physical health with various cycleergometers and hear rate monitors.

- Shared databases.

In addition, the whole redIAPP network has access to an Integrated Database Management System based on a virtual private network which links all the collaborating centres.

The Primary Care Research Unit of Bizkaia, the management centre for the design and analysis of this study, has:

- A user license for SAS statistical package with which all the analyses are carried out.

- Local ICT Infrastructure to undertake training activities and coordination meetings.

- Technical secretarial support.

### Study population

#### Inclusion criteria

• Age ≥ 18 years.

• Diagnosis of HF on the basis of signs and symptoms (Framingham criteria) and evidence of structural heart alterations detected by echocardiography (Echo). Echo scanning guarantees that we are dealing with patients suffering from HF avoiding confounding clinical factors.

• Left ventricle ejection fraction < 45%.

• NYHA functional class II-IV, or Stages B and C of the American Heart Association, in a stable situation for at least the previous four weeks, with no changes in baseline functional status, no signs of congestion or changes in weight faster than 2 kg in three days.

• Receiving optimal treatment with angiotensin converting enzyme inhibitors (ACEI), angiotensin II receptor antagonists (ARA-II), beta blockers, diuretics, and aldosterone antagonists at stable doses for the previous four weeks, as long as there are no justified contraindications for their use, and meeting the clinical practice guidelines of the European Society of Cardiology [1].

• Anticoagulated patients without atrial fibrillation, ejection fraction < 30%, presence of intracardiac thrombi, or history of embolism.

• In cases of sinusal rhythm or atrial fibrillation, ventricular response is under control both at rest and during exercise (90 beats/minute at rest, and 130 beats/minute during moderate exercise).

• Absence of arrhythmia in exercise stress test that would contraindicate exercise.

• Able to attend an exercise programme and travel to the reference laboratory.

• Informed consent confirmed in writing.

#### Exclusion criteria

• Physical and mental comorbidity which preventes undertaking the exercise programme.

• Major cardiovascular events (in the previous 6 weeks) or cardiovascular procedures, including cardiac resynchronization or implantation of a defibrillator.

• Heart failure pending intervention (mitral valve replacement/repair, ventricular reconstruction, pacemaker/resynchronization pacemaker, implantable defibrillator, transplant), given that the procedures greatly change the baseline functional status and the prognosis of the disease.

• Heart failure secondary to congenital heart disease or hypertrophic obstructive cardiomyopathy, given that there is a formal contraindication for exercise in such clinical situations.

• Carrier of a fixed-rate pacemaker.

• Exercise test that contraindicates exercise for safety reasons, especially in the case of exercise-induced arrhythmia.

• Poor cognitive state, depression or psychiatric disorder that prevent adherence to an exercise programme.

• Inability to travelling to the health centre by their own means.

### Recruiting

To recruit patients, the nurse sets up an active surveillance system to identify new HF patients in the health centre. The principal investigator informs the patient about the study, invites them to participate, provides the consent form, makes an initial evaluation, carries out an electrocardiogram (ECG) and registers the information.

### Optimisation of the common treatment for both groups in the study

Once the patient has been recruited, a trained nurse carries out the "optimisation of the treatment". An "information visit" is conducted in which an ECG and a blood sample are requested, and the results of these tests are assessed at the "first medical appointment" with the principal investigator of the health centre. If the patient is "stable" (see discussion) a new "follow up appointment" is scheduled after four weeks with a new prior blood sample. During the stabilisation period, the patient attends five appointments to evaluate prognostic clinical indicators, the battery of health education activities and compliance with non-pharmacological measures. This stabilisation phase lasts for four to six weeks prior to randomisation.

Assessments are made of the patients' cardiac baseline prior to randomisation. In line with this, when the patient is clinically stable, an appointment is made the cardiologist to carry out an exercise stress test, with an echo study and Holter monitor (if clinically required) and the outcome variables are measured.

### Randomisation

This is carried out centrally, once all baseline measurements are taken, by phoning to the Primary Care Research Unit of Bizkaia, where the patient is registered and assigned to one of the two study groups in 1:1 ratio by block randomisation of n patients and stratified by health centres.

### Protocol for the control group

"Optimal therapeutic monitoring appointments" are established at 4, 8, 12, 24 and 48 weeks (1 year), in which clinical assessments made in the first appointment are repeated. In such visits follow-up ECG and blood samples are also required.

### Protocol for the intervention group

The EFICAR group differs from the control group only in terms of the exercise programme, which has two phases. The exercise programme is a combination of "high-intensity interval training" and "muscular strength training". It has been demonstrated that high intensity aerobic exercise leads to better aerobic and cardiovascular changes than light/moderate exercise in patients with HF [13,14].

• *1st PHASE *(12 weeks, 3 sessions/week): for the first three months, patients carry out a progressive exercise programme of 36 sessions under the supervision of the nurse, starting at low intensity (first month) and increasing it month by month (See Figure 2).

**Figure 2 F2:**
[figure not shown]
**Exercise program for the EFICAR group**.

Aerobic training: Aerobic exercise is undertaken on a cycloergometer, including warm-up, conditioning and cool down phase. From the beginning, the exercise sessions are personalised according to the physical condition of each patient. The first month is for "start-up", the second for "progress" and the third for "maintenance". For those patients that are very weak or are not used to aerobic exercise, the first sessions are of light-to-moderate intensity [9,18].

The Borg scale is used to evaluate the "perception of effort" during and after each session (values ranging between 6 and 20). This is a very useful scale to determine intensity with beta blockers, auricular fibrillation, pace-makers or other conditions which may alter the normal response of the heart rate to exercise [19]. The exercise is also monitored with respect to the emergence of symptoms. Aerobic exercise is done before the strength training to guarantee activation of the muscles and cardiovascular system.

Muscular strength training: muscular strength work is a essential aspect of the rehabilitation of patients with HF [15]. To avoid training-related increase of the hemodynamic load the exercise is isotonic. In each session, after 5 min of stretching and 8-12 min of aerobic exercise, six types of exercise are carried out to work various muscle groups: biceps, upper arms and shoulders, knee extensors and flexors, hip flexors and extensors, and plantar flexors. For muscular strength training, weights are used for upper body and resistance bands for the lower body. A different percentage of body weight is applied for each muscular group. Each patient is regularly informed of the progress they have made.

• *2nd PHASE*: The training given in the first phase is intended to ensure that the patients make this exercise part of their routine. They are trained to carry out a type of interval aerobic exercise to they can keep up in their own environment, indefinitely and independently, together with muscular strength exercises. In addition, they are taught how to self-regulate the exercise intensity (Borg Scale, pulsometers, symptoms).

### Outcome measures

These measurements are made by an interviewer blind to the group the patient has been assigned to.

*Primary outcome measure *(basal, 3, 6 and 12 months):

• Changes in health-related quality of life (HRQL) (SF36, Minnesota Living with Heart Failure Questionnaire - MLHFQ).

The HRQL questionnaire is measured blindly with self-administered questionnaires: the Spanish version of the SF-36 and MLHFQ. Both questionnaires will be filled out before and after the intervention. SF-36 generates an 8-dimension health profile and two summary scores for the physical and mental components. The 21 items from the MLHFQ record the perception of the patient in relation to how the HF affects the emotional, social, physical and mental dimensions of their HRQL. Both questionnaires have been validated in the Spanish population [20,21].

*Secondary outcome measures *(basal, 3, 6 and 12 months):

• Functional capacity, measured with the 6-minute Walking Test [22].

• Muscular strength, measured by dynamometry [23].

• Body composition (body fat and muscle percentage) [23].

• Structural changes in the heart (natriuretic peptide levels, prognostic factor) [24].

*Predictor or Confounding variables*: sex, age, comorbidity and risk factors.

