### Sample size

A total of 600 patients will be recruited, 300 per group. This simple size gives a statistical power of higher than 80%, to enable any difference between the control and the intervention group greater than 3 with respect to the primary outcome scale from the physical functioning SF-36 and MLHQ to be found to be significant, with a significance level of 5% using the two-tailed Student's t test (standard deviations obtained from prior studies with similar population to that of our project: SD = 10 points of the quality of life questionnaires SF-36 and MLHQ) [12,25,26]. Given other reports, it can be expected that the losses during follow-up will be around 20%, the correlation between the measurements of the same individual 0.6 and the correlation intracentre 0.01.

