### Statistical analysis

The analysis will be focussed on demonstrating, by analysis of covariance, any improvements at each follow-up, comparing the two groups, adjusted for the baseline level. The effect attributable to the intervention will be estimated by comparing differences in degree of improvement between the groups and the 95% confidence intervals will be calculated. The comparisons will be adjusted for potential confounding factors, by stratified analysis and statistical models, linear for continuous variable outcomes and logistic for dychotomic variables. In order to analyse the overall evolution in the course the one year of monitoring, the time effect on three repeated measures taken for each subject will be estimated, using mixed linear regression models with fixed effects (time, intervention, interaction between time and intervention) and randomised (specific effect of each subject and centre on the baseline level and the effect of time). These models will take into account the longitudinal structure of the three repeated measurements, as well as the hierarchical and multicentre structure of the data. These models will be extended to adjust for hypothetical prediction and modification variables of effect: age, sex, risk factors and comorbidity. All the analysis will be carried out using the SAS statistical package.

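### The plan does not say which score, visit or model decides the primary comparison; if any one significant result may be claimed, the false-positive chance on the two powered scales is about 8-10% or 18-24%, not 5%

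*Protocol article*

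**What the plan says.** - **Outcome.** The abstract states: "The main outcome measure is the change in health-related QoL measured by the SF-36 and the Minnesota Living with Heart Failure Questionnaires". The Outcome measures section repeats this as "Changes in health-related quality of life (HRQL) (SF36, Minnesota Living with Heart Failure Questionnaire - MLHFQ", at "basal, 3, 6 and 12 months". Neither place ranks the two questionnaires or picks a visit. The same section adds that "SF-36 generates an 8-dimension health profile and two summary scores for the physical and mental components".
- **Power.** The Sample size section is narrower. It refers to a difference "greater than 3 with respect to the primary outcome scale from the physical functioning SF-36 and MLHQ", with an SD of 10, 300 patients per group, a two-tailed t test at 5% and power above 80%. It names no visit and does not divide the 5% between the scales.
- **Analysis.** The Statistical analysis section puts ANCOVA first: "any improvements at each follow-up, comparing the two groups, adjusted for the baseline level". It says that "the 95% confidence intervals will be calculated". It then adds a mixed linear model for the course over the year. The abstract mentions only the mixed models. No section says which analysis carries the primary conclusion.
- **Objective.** The main objective speaks of health-related quality of life in general and does not settle the matter.

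**The concern.** Read together, these sections give several primary comparisons and no order among them. Two scales are powered, three post-baseline visits are available, and two kinds of model are planned. The 5% level describes a single test. If more than one test could carry the claim, 5% is not the error rate of that claim.

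This goes beyond a multiplicity method that could be left to an analysis plan. The article does address what is primary, and its outcome, sample size and analysis sections do not arrive at one deciding comparison. A later analysis plan would have to choose among them.

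The point matters more in this trial for two reasons. Participants cannot be blinded and complete the questionnaires themselves. The Background also reports that exercise accounted for less than two points in the largest earlier trial. With a small expected effect on a self-reported outcome, a result that could have been picked from several comparisons would be hard to defend.

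**Working it through.** **Inputs from the Sample size section.** Difference 3, SD 10, 300 per group, two-sided 5%, loss 20% (300 × 0.8 = 240 per group), correlation between measurements of one person 0.6.

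**Step 1: reproduce the stated power.** By the normal approximation, power = Φ(δ / (SD·√(2/n)) − z).
- n = 300: 3 / (10·√(2/300)) = 3.674; 3.674 − 1.960 = 1.714; power 95.7% (t test 95.6%).
- n = 240: 3 / (10·√(2/240)) = 3.286; 3.286 − 1.960 = 1.326; power 90.8% (t test 90.7%).

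The claim of more than 80% is reproduced for one test at 5%.

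**Step 2: count the tests on the two powered scales.**
- One contrast per scale (for example one mixed-model contrast): 2 tests.
- ANCOVA at 3, 6 and 12 months per scale: 2 × 3 = 6 tests.

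**Step 3: correlations.**
- Between visits, from the plan's 0.6: raw scores 0.6; change scores (0.6 − 0.6 − 0.6 + 1) / (2 − 2 × 0.6) = 0.4 / 0.8 = 0.5; baseline-adjusted scores (0.6 − 0.36) / (1 − 0.36) = 0.375.
- Between scales: not in the document. Assumed range 0.3 to 0.8.
- Two tests that differ in both scale and visit: the product of the two correlations.

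**Step 4: chance of at least one false positive, each test at two-sided 5%, no true effect.** With k independent tests this is 1 − 0.95^k. The correlated values come from simulating correlated z statistics (200,000 to 400,000 draws).

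| Reading | Tests | Independent | Correlated, range |
|---|---|---|---|
| One contrast per scale | 2 | 9.75% | 7.7% to 9.6% |
| ANCOVA at three visits per scale | 6 | 26.5% | 17.9% to 24.3% |

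With 0.6 both between visits and between scales, the six-test figure is 20.1%. It does not count the mixed model as a further test.

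**Step 5: power if the error is controlled, 240 per group.**
- 2.5% per scale: 3.286 − 2.241 = 1.045; power 85.2% (t test 85.0%). With ANCOVA and r = 0.6 the SD becomes 10·√(1 − 0.36) = 8, and power is about 97%.
- 5% split over six tests (0.83% each): 3.286 − 2.638 = 0.648; power 74%.

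Naming one contrast per scale keeps the stated power. Splitting the 5% over all six tests does not.

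**The case against.** Four objections deserve an answer.

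1. **No success rule is stated.** A reader might infer that the plan counts any significant score at any visit as a positive trial. It does not say so. The main objective is framed as estimation, and the 5% level appears only in the sample size paragraph. This objection stands. The error rates above are conditional on a selective claim that the plan leaves open, and 5% for each test is inferred from that single level and the 95% intervals. A rule that both scales must be significant on one named contrast would hold the error at or below 5%, but no such rule is given.

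2. **The mixed model may be the main analysis.** The abstract mentions only that model. On this reading there is one test per scale and the error is about 8-10%, so 20% is not a floor. This stands too. However, the Statistical analysis section opens with ANCOVA at each follow-up and does not rank the methods, so the six-test reading is equally open.

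3. **Counting every SF-36 score goes too far.** Eight dimensions, two summaries and one MLHFQ total make 11 scores, or 33 tests over three visits, which a reader might turn into an error of 38-73%. The documents do not support that. The sentence on dimensions describes what the instrument yields, and the Sample size section attaches the word primary to the two powered scales. For the same reason it would be wrong to say that the powered outcome is not the declared one: the powered scales lie within it.

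4. **Error control may sit in an analysis plan.** That is fair for the method, and its absence here is not the point. The deciding score, visit and model belong in the protocol, and the sections shown do not fix them.

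**Conclusion.** The concern holds in a limited form. The protocol article does not fix one deciding comparison for the primary outcome, and its two powered scales share an undivided 5%. If any one significant result on those scales were claimed as primary, the false-positive chance would be about 8-10% with one test per scale and about 18-24% with ANCOVA at three visits.

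These figures rest on an assumed correlation between scales of 0.3-0.8, on correlations between visits of 0.375-0.6 derived from the plan's 0.6, and on testing each comparison at 5%. The sample size itself is not in question.

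**What to change.** Change three sections so that they agree.

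- **Outcome measures:** name SF-36 physical functioning and the MLHFQ total score as the two primary endpoints. Make the other SF-36 scores secondary.
- **Statistical analysis:** name one deciding contrast per scale. It could be the baseline-adjusted difference at 12 months, which is the end of follow-up, or one pre-specified mixed-model contrast. The documents do not favour either, so the sponsor should choose, before any unblinded comparison is seen. Test the two endpoints with Holm or at 2.5% each. Label the other visits and the other model secondary.
- **Sample size:** name the same contrast and restate power at 2.5%: 85% by t test with 240 per arm, SD 10 and a difference of 3.

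The cost is wording only, and no patients are added. The downside is that a benefit seen only at another visit becomes a secondary result.
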